### Sample Size Calculation for Future Full-Scale RCT

A sample size of 25 participants per group is sufficient to measure the proportional outcomes of recruitment efficiency and attrition for each group separately with an SE ≤0.10, assuming no attrition and worst-case variability (0.25) in each group. Past research suggests that attrition of up to 20% is acceptable and limits bias [26,27]. If there is up to 20% attrition in each group, the SE for each proportional outcome will be ≤0.12.

On the basis of Welch 2-sample 2-tailed *t* test, a minimum sample size of 25 participants per group provides 80% power to measure a difference in mean blood pressure and gestational weight change between the intervention and control groups of 0.81 multiplied by the SD, using a significance level of .05 [25]. If there is up to 20% attrition in each group, a difference of 0.91 multiplied by the SD is detectable with 80% power using a significance level of.05 [25]. We will recruit at least 5 additional participants per group, planning for screen failures or participant withdrawals.

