## Methods

### Study Design

This study is a 2-arm prospective RCT and mixed methods evaluation of the PARITY intervention for pregnant Black women. Participants will be randomized to either the information control group (30/60, 50%) or the intervention group (30/60, 50%) in a 1:1 ratio. A sample size of 30 participants per group provides 80% power to detect a significant difference at a .05 level while accounting for attrition [25-27]. Select intervention participants (10/60, 17% to 15/60, 50%) will engage in a qualitative interview at 12 weeks post partum to discuss their experiences, opinions, and suggestions for the intervention. Participants will be enrolled in the study for up to 24 weeks. This time frame will include enrollment, the intervention, and postpartum follow-up assessments. Due to the nature of the intervention, the participants, interventionists, and research assistants will not be blinded. However, standardized training and standard operating procedures, including the use of deidentified self-reported questionnaires administered at baseline and after the intervention period, will reduce the potential for bias due to not blinding.

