### Outcome Measures

At enrollment, participants will sign a medical release of information form allowing the research team to measure data retrospectively from the participant’s medical records. To collect the self-report questionnaires for the enrollment and postpartum assessments, each participant will use a unique, secure link to complete the electronic questionnaires in REDCap at baseline after informed consent is signed and at 6 to 12 weeks post partum based on the participant’s due date. Reminders from the research team will be sent to participants using various forms of contact (phone and email) to complete the questionnaires as needed.

The following outcome measures will be used to examine the feasibility and acceptability of the PARITY intervention:

Feasibility will be assessed through enrollment, attrition, adherence to the intervention, and data collection.Enrollment rate: enrollment will be measured by the percentage of eligible individuals who agree to participate in the trial.Attrition rate: attrition will be measured by the percentage of eligible individuals who complete the study.Adherence to the intervention: adherence to the intervention will be measured using the Intervention Fidelity Checklist, where the doula interventionist will track when contact is made with participants and the number of doula sessions completed. Engagement with the platform will be tracked through clicks and the time spent on the platform.Data collection: data collection feasibility will be measured through study personnel’s sense of ease of use, time required, and missing data.Acceptability of and experiences with the intervention will be assessed using in-depth qualitative information gathered through interviews with intervention participants at 6 to 12 weeks post partum. Interviews will solicit (1) the usefulness of the intervention, (2) ideas to improve the intervention, (3) satisfaction with the intervention, and (4) the utility of innovative technology to deliver the intervention. The qualitative interviews will be audio recorded and transcribed verbatim.

The following outcome measures will be used to examine the preliminary efficacy of the PARITY intervention:

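### The sample-size section attaches its standard errors to a per-group recruitment rate that cannot exist and to an attrition rate with the wrong denominator, and no stated detectable difference matches 30 randomised per arm less 20% attrition

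*Protocol article*

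**What the plan says.** The section Sample Size Calculation for Future Full-Scale RCT carries the figures that support this pilot. On feasibility it describes 25 per group as "sufficient to measure the proportional outcomes of recruitment efficiency and attrition for each group separately". The bound it gives there is a standard error (SE) of 0.10 or less, taking the largest possible variance of 0.25 and no losses. It continues: "If there is up to 20% attrition in each group, the SE for each proportional outcome will be ≤0.12". On efficacy it states that, by a two-sided Welch t test at the .05 level, "a minimum sample size of 25 participants per group provides 80% power to measure a difference in mean blood pressure and gestational weight change" when the true difference is 0.81 SD, or 0.91 SD if 20% in each group are lost. It then adds at least five more per group for screen failures or withdrawals.

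Outcome Measures defines the recruitment outcome: "enrollment will be measured by the percentage of eligible individuals who agree to participate in the trial". The same list defines attrition over eligible individuals too, and counts those who finish rather than those lost. Recruitment and Participant Allocation describe a single recruitment route, with group assignment only after consent and completion of the baseline surveys.

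Study Design fixes 60 participants, 30 per arm, and states: "A sample size of 30 participants per group provides 80% power to detect a significant difference at a .05 level while accounting for attrition".

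**The concern.** Feasibility is the first objective, and the pilot is meant to inform a larger trial. The precision statement should therefore describe quantities that the trial can measure, at the number it randomises. It falls short in three ways.

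- **Recruitment.** Someone who declines is never allocated, so a recruitment proportion cannot be computed by group, and its denominator is the pool of eligible people.
- **Attrition.** Participants who leave are the events being counted. Removing them from the denominator treats attrition as an outcome observed only in completers.
- **Detectable difference.** The stated values are for 25 and 20 analysed per group. Neither is 30, nor 30 less the plan's own 20%. The one sentence that ties power to 30 per group gives no effect size and no outcome.

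At stake are the coherence of the precision justification and the way the power sentence will be read. The size of the trial is not in question.

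**Working it through.** **Inputs.** From the sample-size section: 25 per group, variance 0.25 for a proportion (p = 0.5), 20% attrition, two-sided alpha .05, 80% power. From Study Design: 30 randomised per arm, 60 in all.

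**1. Reproduce the stated SEs.** SE = sqrt(p(1−p)/n).
- n = 25: sqrt(0.25/25) = 0.100, as stated.
- 20% lost from 25 leaves 20: sqrt(0.25/20) = 0.112, consistent with the stated bound of 0.12.

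The rise from 0.10 to 0.12 therefore comes from cutting the denominator from 25 to 20.

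**2. Attrition with its proper denominator.** All randomised participants count.
- 30 per arm, worst case: sqrt(0.25/30) = 0.091.
- 30 per arm, 20% attrition: sqrt(0.20 × 0.80/30) = sqrt(0.16/30) = 0.073.
- Even at 25 per arm: 0.100 worst case and sqrt(0.16/25) = 0.080 at 20%.

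The like-for-like worst-case comparison is 0.091 (n = 30) with the stated 0.10 (n = 25). The 0.073 uses p = 0.20, so it should not be set directly against the worst-case 0.12. Counting completers instead of losses leaves the SE unchanged, because p(1−p) is symmetric.

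**3. Recruitment.** There is one overall proportion, with SE = sqrt(p(1−p)/N) and N the number of eligible people. The documents give no expected uptake, so a range is assumed. If 60 enrol at uptake p, then N = 60/p.

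| Assumed uptake | Eligible N | SE |
|---|---|---|
| 30% | 200 | 0.032 |
| 50% | 120 | 0.046 |
| 70% | 86 | 0.049 |

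Substituting N = 60/p gives SE = p × sqrt((1−p)/60), which is largest at p = 2/3: 0.667 × sqrt(0.333/60) = 0.050. With 60 enrolled, the SE is at most about 0.05 whatever the uptake.

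**4. Detectable differences.** Two-sided two-sample t test with equal group sizes, 2n−2 degrees of freedom and noncentrality d × sqrt(n/2), solved for 80% power:

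| Analysed per arm | Difference (SD) | Where it stands |
|---|---|---|
| 20 | 0.909 | stated as 0.91 |
| 24 | 0.826 | not stated |
| 25 | 0.809 | stated as 0.81 |
| 30 | 0.736 | not stated |

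Both stated values reproduce. Starting from 30 randomised, 20% attrition leaves 30 × 0.80 = 24. At 24 per arm, power for 0.81 SD is 78.4%; at 30 with no loss it is 87.0%. Falling from 30 to 20 would take a loss of 10/30, or one third.

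**5. The power sentence.** Study Design ties 80% power to 30 per group allowing for attrition. The difference that matches this under 20% attrition is 0.83 SD, which appears nowhere. The sample-size section limits its calculation to mean blood pressure and gestational weight change; Study Design does not repeat that limit.

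**The case against.** The strongest reply is that nothing stated is numerically false. The SEs are given as upper limits, and they hold: attrition is at most 0.091 and recruitment about 0.05. The section calls 25 a minimum and discloses the five extra per group. Planning on a minimum and over-recruiting is ordinary practice. The value for 24 analysed, 0.83 SD, lies between the two printed ones and only 0.02 SD from the first; 78% against 80% power is a small gap. Study Design is a summary sentence, and a reader can find effect sizes, test and outcomes later in the article.

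Most of this stands, and it limits the point. Three stronger readings are tempting, and the documents do not support them:
- *The stated bounds are exceeded, or the trial is underpowered on its own terms.* The misapplication is conservative, and 24 analysed gives more than 80% power at the stated 0.91 SD.
- *The 80% power extends to cesarean birth.* The sample-size section claims power only for mean blood pressure and weight change. The documents also give no control cesarean rate from which power could be worked out.
- *The five extra per group were meant to absorb 20% attrition and fall short.* The section assigns them to screen failures or withdrawals and treats 20% attrition separately through the 0.91 SD figure.

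The reply does not rescue a per-group recruitment proportion, or an attrition SE that grows because people drop out. Nor does the cross-reference fully repair Study Design, because the later section gives no difference for 30 randomised or 24 analysed.

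**Conclusion.** The point holds as a misapplication in the conservative direction. The arithmetic is right for the sample sizes used, but it is attached to a recruitment quantity that has no per-group value and to an attrition proportion whose denominator cannot shrink. For the trial as designed, the attrition SE is at most 0.091 per arm and 0.073 at 20% attrition. The recruitment SE is about 0.03 to 0.05 for assumed uptake of 30% to 70% with 60 enrolled. The 80%-power difference after 20% attrition is 0.83 SD.

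This rests on two readings. Recruitment efficiency is not itself defined, so it is taken to be the enrollment rate in Outcome Measures. Attrition is taken as a proportion of those randomised, which is the only reading that gives it a value for each group. The Outcome Measures definition, based on eligible individuals, does not yet say that. No change to sample size, design or analysis follows.

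**What to change.** In the sample-size section:
- Give recruitment as a single overall proportion of eligible people, with SE sqrt(p(1−p)/N eligible).
- Give attrition as a proportion of the 30 randomised per arm, with SE at most 0.091 (0.073 at 20% attrition).
- State that 24 analysed per arm, meaning 30 randomised less 20%, gives 80% power for a 0.83 SD difference in mean blood pressure or gestational weight change.

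In Outcome Measures, redefine attrition over randomised participants so that it matches that denominator, and say whether it counts those lost or those who complete.

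In Study Design, add the 0.83 SD and the two outcomes to the power sentence.

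The cost is restated text only. No participants are added. The power statement will read as more limited than it does now.

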## Results

This pilot RCT is funded by the National Institute of Nursing Research. Data collection was initiated in August 2023 and will continue for approximately 2 years. We will report on the outcomes identified above in a peer-reviewed journal. We anticipate that the results of this feasibility RCT will inform a larger RCT with a 12-month version of PARITY.

## Discussion

### Overview

This pilot RCT and mixed methods evaluation will provide information on the feasibility, acceptability, and preliminary efficacy of the PARITY intervention in Black pregnant women, as well as provide critical information on study design, retention, effect sizes, and outcomes assessment. We anticipate finding improvements in maternal blood pressure, gestational weight gain, and cesarean birth rate in the PARITY program intervention group compared with the information-only control group. In addition, we expect that focusing on strengths and leveraging them during pregnancy will improve wellness behaviors and empowered strength variables, such as adherence to medical care and appointment compliance.

Previous work seeking to understand the mechanisms of Black maternal health disparities have characterized the negative outcomes experienced by Black women as socioeconomic in nature [55,56]. While these factors are associated with maternal morbidity and mortality, Black maternal health disparities cannot be explained entirely by factors such as income, educational level, and health insurance status [7,9]. Further, this narrative is problematic, as it reinforces the stereotype that Black women have low income and are undereducated [57,58]. Indeed, our previous work involving nearly 10,000 nulliparous mothers showed that Black women with higher education and adequate income were more likely to experience maternal morbidity than their counterparts of other racial or ethnic backgrounds who had lower education and income levels [59]. A growing body of evidence suggests that disparities in Black maternal health outcomes are not rooted in biology. Instead, discrimination and bias due to race are driving contributors to the decreased rates of prenatal care, reduced quality of care, and poor health outcomes for childbearing women of color [60-62]. The failure of prior research to ameliorate maternal health disparities may be related to the prevailing deficit-based framework through which maternal health research is designed and disseminated [9].

### Strengths

This research study uses the following strategies to work on overcoming deficit discourse through a strengths orientation: (1) includes a focus on capabilities, strengths, and opportunities; (2) conducts research with and by instead of about the individuals or groups; (3) promotes hope by using language that is person centered and optimistic and leads to positive perceptions; (4) identifies social context and the resources that exist within communities; (5) includes research questions that lead to empowerment; and (6) engages research participants with respect, allowing opportunities in which they offer their expertise about their situation [16].

In addition, current maternal health research rarely focuses on how Black women can become or remain well. Along with health care adherence, wellness includes daily lifestyle habits, such as physical activity, nutrition, sleep, and connectedness, that promote optimal physical and mental health. Our previous work showed that simple wellness-related lifestyle changes, such as physical activity, improved nutrition, and better sleep, were associated with decreased pregnancy complications [52]. Despite being largely ignored in the severe maternal morbidity research literature, wellness strongly impacts maternal outcomes. Daily wellness habits focused on physical activity, nutrition, and sleep are easier for pregnant women to implement compared to complex interventions and have the potential to increase the lifelong health of women and their families. This intervention is designed to work on building strong daily wellness habits and to empower women with the knowledge and tools to make healthy choices.

This research offers a comprehensive, innovative approach to improving maternal wellness by integrating a strengths-based framework, novel technology, and peer-based community support while addressing access to care, quality of care, and each participant’s social needs and strengths. This research has the potential to provide pragmatic solutions for Black maternal disparities and shift the narrative about Black women in the research literature. Knowledge gained from this research may inform future research and practices related to community-engaged approaches and interventions.

### Challenges and Limitations

Due to the nature of pregnancy and the inexact times during which birth occurs, we expect that participants will receive varying doses of the intervention. This is a limitation of pregnancy-related research and will be accounted for in analyses. In addition, limitations on funding make it so that we cannot translate materials into other languages or provide translators for this feasibility study, limiting the population to English-speaking individuals. The intervention evaluated in this study requires participants to own a smartphone, which also limits the population that can be reached in this study. Finally, several measures obtained at the 4 main data collection time points might burden participants or lend themselves to missing data.

### Conclusions

Integrating a unique technology intervention alongside doula support represents a novel approach to maternal health interventions. This research will inform the feasibility of conducting a larger study and other future research involving community-engaged approaches. Moreover, the results hold promise in combating deficit discourse surrounding Black maternal populations, both within academic and clinical settings. By focusing on empowered wellness and leveraging strengths, this intervention aims to reduce maternal health disparities in Black women. The anticipated outcomes of this study will shed light on the effects of the PARITY intervention in addressing these disparities and may illuminate the role of individual protective assets in buffering against maternal health inequities.

## Appendix

Multimedia Appendix 1 Peer review report.

## Abbreviations

CHW: community health worker
GLMM: generalized linear mixed model
IPAQ-SF: International Physical Activity Questionnaire-Short Form
IRB: Institutional Review Board
ISR: Index of Self-Regulation
MET: metabolic equivalent of task
PARITY: Protective Assets Reinforced With Integrated Care and Technology
PMM: pattern-mixture model
PSI: Problem-Solving Inventory
RCT: randomized controlled trial
REDCap: Research Electronic Data Capture
SMI: Self-Motivation Inventory
